## Abstract

**Introduction:**

Keratinocyte cancers (KCs) are increasing in incidence in the UK, with over 234 000 cases annually, largely due to demographic changes and sun exposure. Skin cancers, including malignant melanoma and KCs, are projected to cost the NHS over £180 million annually and impose healthcare demands. Although KCs have high cure rates following surgical excision and primary closure, wounds healing by secondary intention (HBSI) particularly on the lower leg present clinical challenges. Compression therapy (CT) known to improve venous insufficiency and venous ulcer healing may also benefit HBSI following lower limb KC excision but current evidence is sparse.

**Methods and analysis:**

**H**ealing of **E**xcision**A**l wounds on **L**ower legs by **S**econdary intention (HEALS2) is a multicentre, prospective, Phase III, parallel group, open-label, randomised controlled trial with embedded internal pilot and blinded endpoint assessment. A total of 396 participants (≥18 years) from UK skin cancer surgery centres will be randomised 1:1 to assess the clinical and cost-effectiveness of standard care (SC) alone or with CT (SC+CT) for surgical wounds HBSI following excision of lower limb KCs.

The primary outcome is time to healing from randomisation (maximum 52-week follow-up). Secondary outcomes include incidence of infection, antibiotic usage, scar quality, safety (including complications and hospitalisations), quality of life, cost-effectiveness and relationship between post-partial closure wound area, type of partial closure method and time to healing. Exploratory objectives include association between short-term wound area reduction and time to HBSI, patient acceptability, adherence and associations between wound breakdown post-healing and CT use. A qualitative sub-study will explore patients’ experiences and decision-making during CT use.

Primary endpoint analysis will be conducted on the intention-to-treat population using a multivariable Cox Proportional Hazards modelling. Secondary outcomes and safety will be evaluated using other regression models and descriptive statistics, respectively. Cost-effectiveness will be evaluated using within-trial analysis and decision-analytic modelling. Patient and public involvement representatives are contributing to trial design and oversight. The study protocol complies with the Standard Protocol Items: Recommendations for Interventional Trials (SPIRIT) Statement.

**Ethics and dissemination:**

Ethics approval has been granted by the Yorkshire & The Humber – Leeds East Research Ethics Committee (ref 23/YH/0247). Findings will be published in high-impact peer-reviewed journals.

**Trial registration number:**

ISRCTN12417689.

STRENGTHS AND LIMITATIONS OF THIS STUDYA multicentre randomised controlled trial investigating the effects of adjunctive compression therapy (CT) in patients following surgical excision of keratinocyte cancer (KC) and healing by secondary intention.Study includes patients’ perspective of the experience of CT post-surgical excision of KC.Pragmatic trial with choices of evidence-based CT that consider patient abilities and lifestyles and accommodate different local clinical pathways.Limited to patients with secondary intention healing (excludes those who have primary closure, flap or graft).Limited to those who have a suspected KC (non-KCs for example, melanoma usually experience a different clinical pathway).

## Introduction

 Skin cancers are common with numbers increasing yearly due to demographic changes, for example, an increasingly aged population and social changes including levels of sun exposure.^1^ Skin cancers, including malignant melanoma and keratinocyte cancers (KCs), in the UK are projected to cost the NHS over £180 million per year and impose significant demands on primary, community and secondary care services.^2
3^ KCs, including basal cell and squamous cell carcinomas, are very common (annual incidence of over 234 000 cases)^4^ but have high cure rates with surgical excision and primary closure/skin graft/flap or partial/no closure and healing by secondary intention (HBSI).

Surgical wounds healing after excision of KC lesions on the lower leg provide particular clinical challenges. First, due to anatomical location and lack of skin laxity, many are not amenable to primary closure.^5^ Second, people undergoing surgery for KC on the lower leg are typically elderly with concurrent mobility limitations, peripheral vascular disease and local oedema, factors which delay healing and increase risk of complications including infection.^6
7^ Thirdly, postoperative oedema due to the inflammatory process is a common sequela of surgical wounds which normally resolves within a few days in most body sites. However, in the lower leg, the cumulative effect of peripheral vascular/venous disease and gravity delays this resolution and is likely to compromise wound healing.

The annual prevalence of acute and chronic wounds increased by 71% between 2012/13 and 2017/2018, with an estimated 3.8 million patients with a wound (excluding surgical wounds healing within 4 weeks) managed by the National Health Service (NHS) in 2017/18 and an annual cost of £8.3 billion.^8^ Surgical wounds (of over 4 weeks) accounted for 14% of these wounds, and in turn those on the lower limb account for 15% of all surgical wounds HBSI.^7^ Wounds HBSI impact on quality of life, with considerable patient burden due to pain, exudate, repeated visits for wound dressings, possible infections and inability to work and/or socialise with long term effects of scarring and discomfort.^9^

In considering this patient cohort and common condition, three factors impeding understanding of best practice were identified: a lack of outcome data as patients are usually discharged from secondary care follow-up before healing, an absence of a recognised guideline for the postoperative management and clinical uncertainty about the use of compression as a primary postoperative intervention to promote time to healing and reduce complications.

The lack of evidence to underpin practice was acknowledged by the UK Dermatology Clinical Trials Network (UKDCTN) who supported a programme of research to inform this grant application. The work has included: a 2014^5^ and 2021 survey of clinicians;^10^ UKDCTN-funded trainee-led cohort feasibility study;^11
12^ UKDCTN patient and public involvement (PPI) focus group and a trainee-led systematic review^6^ as detailed in the following sections.

### Patient burden

The UKDCTN-funded Healing of ExcisionAl wounds on Lower legs by Secondary intention (HEALS) cohort study (n=53) was undertaken to assess the feasibility of performing a large-scale definitive phase III trial and is the first study to investigate time to healing, infection and serious adverse events (SAEs) following excision of KC on the lower leg and HBSI in patients without compression.^11
12^ The cohort study recruited from nine centres across the UK. Participants were adults, without significant arterial disease (ABPI ≥0.8), who had planned excision of KC on the lower leg and expected to have a wound HBSI without postoperative compression.

Participants and non-registered patients shared similar demographic characteristics, demonstrating that the sample was representative of the target patient population. Patients received routine follow-up care and data was collected weekly either at standard care (SC) clinic visits or phone calls. Variables collected postoperatively included details of clinical assessments, wound treatments, medications and healing status. Patient pathways were characterised by the frequency of clinical visits, type of professional and care setting for follow-up contacts.

The study population had a median age of 81 years. 21% had mobility limitations and while patients with severe arterial disease (ABPI <0.8) were excluded, 73.6% had visible or palpable signs of venous disease. Reflecting risk factors for delayed wound healing, the study identified considerable patient and NHS burden with median time to healing 81 days (95% CI 73 to 92), incidence of wound infection 30.2% (n=16), hospitalisation for infection/cellulitis 5.7% (n=3), unhealed at 6 months 7.5% (n=4) with healing status unknown at 6 months post-surgery for 7.5% (n=4).^11^

### Evidence for compression therapy and knowledge gap

Compression therapy (CT) has been established by primary research/systematic review evidence as the primary/first-line treatment strategy for healing of venous leg ulcers (VLUs). The VenUS trials have also helped inform which compression systems are most effective.^13
14^ Compression is now commonly used for the treatment of VLUs where it has transformed management, thereby reducing the burden of wounds.

Mechanistically, compression reduces oedema and improves venous return and tissue oxygenation. Given the high levels of underlying venous disease and the normal occurrence of postoperative oedema due to the inflammatory process it is proposed that lower leg surgical wounds HBSI may benefit from compression in a similar manner. However, it is also recognised that CT can be resource intensive (although the use of compression hosiery is now enabling patient self-care) and can sometimes be difficult to apply and uncomfortable for the patient. When our patient group were presented with different compression options, most members agreed that bandages might be hot and/or uncomfortable, but those who had experienced oedema/infection or delayed healing were less concerned with these issues.^12
13^

We conducted a systematic literature review^7^ and did not find any randomised controlled trials (RCTs) comparing no compression with compression for wounds HBSI after excision of KC on lower leg. We identified only two cohort studies with reported median time to healing for no compression (n=53) of 81 days^12^ and mean time to healing with compression (n=10) of 50 days.^15^ Unpublished local audit data at a participating centre also reported 88% (22/25) of patients with compression healed within 6 weeks. From a safety perspective, we also identified a retrospective cohort n=366^16^ which reported that patients who had postoperative compression were less likely to develop complications versus those without compression (OR 0.67: p=0.74), but time to healing was not reported.

CT has been rigorously evaluated in the VLU population^17^ with significant evidence that it increases healing rates when compared with no compression, with improved time to healing (five studies; 733 participants; HR 2.17 (95% CI 1.52 to 3.10)) and complete healing (eight studies; 1120 participants: relative risk/risk ratio (RR) 1.77 (CI 1.41 to 2.21)) with no impact on adverse events (AEs).^14^ Systematic review evidence and trials also indicate that: multi-component systems are more effective than single component systems; elasticated systems are more effective than non-elastic, and within Class bandage systems and hosiery are similarly effective, for example, 4-layer bandage, 2-layer bandage and 2-layer hosiery^18^ which has improved patient and clinician choice and associated adherence. For example, the most recent Health Technology Assessment study^13^ found no difference in healing between (Class 3) 4-layer high compression bandaging or 2-layer hosiery, while hosiery was easier to apply, less bulky and use more likely to be sustained.

Based on the perspective of the VLU patient population, there is evidence that some patients do not always adhere to their CT. A qualitative study has been recently published which explored barriers and facilitators to CT.^19^ Findings suggest that adherence is multi-factorial with issues such as the choice of therapy, patient lifestyle and service organisation being contributing factors.

CT is sometimes applied to reduce leg oedema and promote healing for lower limb KC wounds HBSI, but there is clinical equipoise, variation in practice when used and no supporting evidence of effectiveness. Our PPI work has also shown that compression is acceptable to this group of patients. Given the findings from the literature, the feasibility study and with the similarities with mechanistic mode of action in venous conditions, it is therefore essential to assess the clinical and cost-effectiveness of compression as a primary postoperative intervention in terms of reduced time to healing and secondary outcomes including infection.

## Objectives

The aim of this pragmatic RCT is to evaluate the clinical and cost-effectiveness of SC+CT in the healing of surgical wounds HBSI following excision of lower limb KCs.

### Primary objective

To compare the time to HBSI from randomisation, between SC and SC+CT.

#### Secondary objectives

To compare groups for:

Incidence of infection as measured by modified Bluebelle Wound Healing Questionnaire (WHQ)^20^ until healing.Numbers of days participants prescribed antibiotics until healing.Scar quality as measured by Patient and Observer Scar Assessment Scale (POSAS).^21^Safety events including related complications and hospitalisations until healing (maximum 52 weeks post randomisation).Cost-effectiveness via a within-trial analysis and decision analytic model (DAM) assessed from a payer perspective measuring patient health-related quality of life in terms of Quality Adjusted Life Years (QALYs) meeting updated Consolidated Health Economic Evaluation Reporting Standards (CHEERS) 2022 updated reporting guidance.^22^Resource use and health-related quality of life (HRQoL) as measured by EuroQol 5 Dimensions 5 Levels questionnaire (EQ-5D-5L) to 26 weeks post randomisation (52 weeks where applicable, for unhealed participants only).The relationship between post-partial closure wound area, type of partial closure method, and time to healing.

### Exploratory objectives

These include exploring:

Associations between short-term wound area reduction between baseline and 4 weeks post randomisation and time to HBSI.Patient acceptability and factors affecting adherence to randomised treatment.Associations between wound breakdown post healing and the use of CT.

### Qualitative sub-study objectives

These include understanding and assessing:

Challenges and difficulties encountered during CT.Impact of CT on daily activities and quality of life.Patients’ satisfaction with the support provided.Factors influencing patients’ decisions to continue or discontinue CT.

## Methods

HEALS2 is a multicentre, prospective, Phase III, parallel group, open-label, RCT with embedded internal pilot, blinded endpoint assessment, economic evaluation, minimum 26-week/maximum 52-week follow-up, comparing time from randomisation to complete surgical wound healing (epithelialisation) by secondary intention between control (SC) and intervention (SC+CT) groups (see study design illustrated in figure 1). The qualitative sub-study entails virtual semi-structured interviews with participants randomised to CT. These will be audio-recorded, transcribed and analysed.

**Figure 1 F1:**
[figure not shown]
Flow diagram of HEALS2 study design. AE, adverse event; CTRU, Clinical Trials Research Unit; EQ-5D-5L, 5-Level version of EuroQol 5-Dimensions Questionnaire; KC, keratinocyte cancer; POSAS, Patient and Observer Scar Assessment Scale; SAE, serious adverse event; WHQ, Wound Healing Questionnaire.

### Eligibility

All adult patients attending a UK secondary care skin cancer surgery centre (SCSC) will be screened for suitability according to the eligibility criteria (box 1), by the attending clinical/research team if they have a suspected KC on the lower leg which is planned to be excised and HBSI. The lower leg is defined as ‘below the knee, including the ankle and foot but excluding the toes’. Patients will be consented preoperatively. Screening logs will be maintained to review reasons not eligible or unable/declined consent and to demonstrate the representativeness of the study sample.

Box 1Eligibility criteriaInclusion criteriaAged ≥18 years.Planned excision of suspected keratinocyte cancer (KC) on lower leg with healing by secondary intention.Ankle-brachial pressure index ≥0.8 or toe pressure of >60 mm Hg (measurements taken within 3 months of randomisation).Informed written/witnessed verbal/eConsent.Exclusion criteriaPlanned primary closure/skin graft/flap.Receiving/planned compression for another indication.Severe venous incompetence, for example, Clinical-Etiology-Anatomy-Pathophysiology classification C5 or C6.^43^Contraindication to at least medium compression (18–24 mm Hg).Unable to comply with CT.Suspected to have a non-KC diagnosis or require further surgery.Previously taken part in Healing of ExcisionAl wounds on Lower legs by Secondary intention (Phase 2).

### Recruitment/consent

The trial will recruit participants from SCSCs including district general and teaching hospital settings. The recruitment centres may comprise dermatology surgery and/or plastics surgery services with surgery scheduled in outpatient clinic and day case surgery facilities. Research centres will be required to have obtained local confirmation of capability and capacity, undertake a site initiation meeting with the Clinical Trials Research Unit (CTRU) and receive a CTRU green light prior to the start of recruitment into the trial.

Informed consent will be obtained prior to the participant undergoing procedures that are specifically for the purposes of the study. The right of a participant to refuse participation or withdraw at any time from the study without giving reasons will be respected. Informed consent can be taken either (a) As remote e-consent, (b) Remote verbal consent over the telephone/video calling and (c) Face-to-face during an SCSC visit on a paper form or using an e-consent format. The mode of informed consent used will depend on patient and participating site preference, and their accessibility to a device to support the e-consent process. Patients will be provided with information on the e-consent process to help inform their decision on the method of consent.

For the qualitative sub-study, the target population will be patients randomised to the CT arm of the main trial and who have undergone or are currently undergoing CT. The patients will be those who have opted into the sub-study.

Patients are referred from a healthcare professional to an SCSC, reflecting the variation in referral, diagnosis and surgical scheduling. The referral will usually suggest a potential diagnosis of a KC on the lower leg and be accompanied by photographs. Several pathway options may then be available for identifying eligible participants depending on local arrangements. Identification can occur during telephone/video or face-to-face diagnostic assessment and scheduling of surgery as part of the routine clinical care or where potential trial eligibility (ie, suspected KC on the lower leg and planned HBSI) is observed.

*NB* If a patient consents with the expectation that the wound will be HBSI but surgery is completed with primary closure, then randomisation will not take place. The likelihood of this happening will be explained to the patient during the informed consent process.

### Randomisation

Randomisation will take place immediately postoperatively (in theatre or postoperative recovery area). 396 participants will be randomised in a 1:1 allocation ratio (198 per group) to SC or SC+CT stratifying by:

Centre.Immediate post-excision wound area (6.0 cm^2^ or less/more than 6.0 cm^2^ prior to any partial closure).^23^Wound depth (excision to fat/excision to fascia or periosteum).

Randomisation will be performed via a central, independent, secure 24-hour automated randomisation system provided by Leeds CTRU using a minimisation algorithm (including a random element) to ensure allocation concealment.

### Post-randomisation re-excision of wound

In the event that a patient undergoes further surgery on their wound, they will continue in the trial unless the wound is no longer HBSI, for example, primary wound closure or the application of a skin flap or graft. Patients will be clinically withdrawn at this point and no further data collected.

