If the wound is assessed as unhealed at the confirmation of healing visit, a photograph will be taken, and routine weekly/monthly phone calls and randomised treatment will be reinstated.

Medical record review will be undertaken at 26 and 52 weeks (where applicable, if not healed at 26 weeks) to capture related SAEs (including hospitalisations and related infections) and date patient last known to have an unhealed wound. Record review to also be performed on an ad-hoc basis if the participant dies, withdraws or is lost to follow-up.

The following information will be recorded:

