#### Primary analysis of primary outcome measure

Primary analysis of the primary outcome measure, time to complete healing will be conducted on the intention-to-treat population using a multivariable Cox Proportional Hazards (PH) regression model adjusted for the minimisation factors post-excision wound area and wound depth; the potential for fitting centre as a random effect will be explored. Re-excision will be considered as a time-dependent covariate. Estimated HR will be presented with 95% CI and significance. Unadjusted Kaplan-Meier plots and estimates of survival functions (where ‘survival’ corresponds to *healing not observed*) and the stratified log-rank test statistic and its significance will be also reported. Should the PH assumption appear to be violated, an appropriate alternative analysis method will be used.

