#### Sensitivity analyses

*Death as a competing risk*: should incidence of death be substantial as a competing risk event, a multivariable Fine & Grey regression model^28^ adjusted for the minimisation factors may be fitted to the primary outcome measure.*Treatment adherence*: patterns of treatment adherence will be explored, and an appropriate statistical method taking adherence into account while respecting the randomisation (eg, rank preserving structural or structural nested failure time model^29–31^ or marginal structural model)^32
33^ will be used to model causal treatment effect for observed adherence.*Alignment with Health Economic analysis*: a parametric model consistent with that which is required in the health economic analyses (see Economic Evaluation section) for providing transition probabilities beyond the time frame of the trial will be fitted to the primary outcome measure.

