#### Missing data considerations

The extent of missing data for each primary and secondary endpoint will be presented by trial arm along with reasons where available. Missing data strategies appropriate for each primary and secondary analysis will be employed. For example, should primary endpoint censoring appear informative, inverse probability of censoring weighting may be used. Further details on how missing data will be handled in each analysis are included in the SAP.

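### The protocol ends all data collection when a wound is later closed, flapped or grafted, although consent stands; this sits badly with the intention-to-treat label and the record review, and loses cost-utility data to week 26

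*Protocol article*

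**What the plan says.** The section on post-randomisation re-excision says that participants who have more surgery on the wound stay in: "they will continue in the trial unless the wound is no longer HBSI". Primary closure, flap and graft are its examples of the exception. For these: "Patients will be clinically withdrawn at this point and no further data collected".

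Four other places bear on this:

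- **Primary objective:** "To compare the time to HBSI from randomisation, between SC and SC+CT". Closure, flap or graft makes that event impossible.
- **Primary analysis:** it "will be conducted on the intention-to-treat population using a multivariable Cox Proportional Hazards (PH) regression model". On further surgery it adds only: "Re-excision will be considered as a time-dependent covariate".
- **Sensitivity analyses and missing data:** a competing-risk model is planned for one event, "should incidence of death be substantial as a competing risk event". Separately, "should primary endpoint censoring appear informative, inverse probability of censoring weighting may be used".
- **Assessments and data collection:** "Record review to also be performed on an ad-hoc basis if the participant dies, withdraws or is lost to follow-up". The week 52 data collection section repeats this requirement.

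**The concern.** The protocol itself, not the participant, ends observation, and it does so because of a clinical event after randomisation. Treatment is open-label; only assessment is blinded. Whether to close or graft may therefore depend on the arm or on how the wound is doing. Intention-to-treat normally means following everyone as randomised as far as consent allows, and this rule does the opposite for one outcome-defined group.

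The clearest loss is in the economic evaluation. The within-trial analysis runs to 26 weeks. A participant whose wound heals at week 10 is still asked for EQ-5D-5L and resource use at weeks 12 and 26. One whose wound is grafted at week 10 is asked for nothing more, although the extra procedure and its aftermath carry costs and affect quality of life. If the rates of such surgery differ by arm, so does the missingness.

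The primary hazard ratio could also be affected, because these participants would probably be censored at surgery. That is harmless only if, given the covariates, surgery is unrelated to the healing the wound would otherwise have shown.

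**Working it through.** **1. Which data are lost.** At weeks 12 and 26 the article limits the modified Bluebelle questionnaire to unhealed participants but puts no such limit on EQ-5D-5L or resource use. The secondary objectives agree: both run to 26 weeks, and only the 52-week extension is confined to the unhealed.

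| Participant | EQ-5D-5L and resource use, weeks 12 and 26 |
|---|---|
| Healed | collected |
| Still unhealed | collected |
| Closed, flapped or grafted earlier | not collected |

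The four Markov states (healed, unhealed, infected, dead) include none that is plainly meant for the third row.

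**2. The conflict over record review.** The re-excision section allows no further data. The assessments section requires a record review when a participant withdraws. If clinical withdrawal counts as withdrawing, the two conflict. If it does not, these participants get no review at all. Sites cannot tell which applies. Even when done, the review covers related serious events (including hospitalisations and related infections) and the date the wound was last known unhealed, not questionnaires.

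**3. The plan's own sample size.** Inputs from the sample size section: medians 81 and 57 days, two-sided 5%, 90% power, 10% attrition, 396 randomised.

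- Hazard ratio 81/57 = 1.421, log 0.3514.
- Schoenfeld events: 4 × (1.960 + 1.282)² / 0.3514² = 341.
- Probability of healing within follow-up (exponential; 52 weeks for most, 26 to 52 weeks for the last 6 of 31 recruitment months): 0.963.
- 341 / 0.963 gives 355; 355 / 0.90 gives 395, against 396 stated. The figure reproduces.

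**4. Power.** The article gives no rate of later closure, flap or graft, so 5% and 10% are assumed, on top of the 10% attrition.

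- Base: 396 × 0.90 = 356 participants; 356 × 0.963 = 342.8 events.
- 5% closed: 342.8 × 0.95 = about 326 events. With z = √326/2 × log HR − 1.960, power is 0.89 (HR 1.421) to 0.90 (HR 1.43).
- 10% closed: 342.8 × 0.90 = 308.5 events; power 0.87 to 0.88.

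**5. Bias in the hazard ratio if they are censored at surgery.** Simulation with exponential healing, control median 81 days, surgery between days 56 and 84, Cox model on arm, 400,000 participants per scenario. Rates of surgery of 2% to 10% are assumed.

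| Who has surgery | True HR | Closed, SC / SC+CT | Estimated HR |
|---|---|---|---|
| Unrelated to healing speed | 1.43 | all pairs tried, 2% to 10% | 1.41 to 1.44 |
| Unrelated to healing speed | 1.00 | all pairs tried, 2% to 10% | 0.99 to 1.01 |
| Very slowest in each arm (extreme bound) | 1.43 | 2/2, 5/5, 10/10% | 1.51, 1.57, 1.65 |
| Very slowest (extreme bound) | 1.43 | 10/5% | 1.42 |
| Very slowest (extreme bound) | 1.43 | 5/10% | 1.74 |
| Very slowest (extreme bound) | 1.00 | 10/5% | 0.84 |
| Very slowest (extreme bound) | 1.00 | 5/10% | 1.18 |

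A milder model (Weibull shape 1.6, frailty variance 0.5, surgery confined to the slowest quarter) moves a marginal HR of 1.28 down to 1.24 when 7.5% of SC and 2.7% of SC+CT are closed. Neither direction nor size can be presumed.

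Keeping closed wounds in the risk set as never healed by secondary intention gives 1.32 to 1.33 for a true 1.43 at 5% in both arms. That answers a different question; it is not the corrected value of the same one.

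**The case against.** A reader might infer that the rule removes the worst healers from the primary analysis. The article does not say so. The section is about re-excision and gives no reason for the surgery, which could be tumour clearance: histology is collected during follow-up. (Patients suspected at entry of needing further surgery are excluded, but that does not settle later reasons.) Nor does any section take these participants out of the intention-to-treat set. Their time before surgery can still count, and data already held are kept even when consent is withdrawn. Censoring is the likely default, not a stated rule. These points stand.

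A reader might also infer that the model can only censor them as average healers. The missing-data section allows inverse probability of censoring weighting. It is optional and works only if measured covariates explain the surgery, but it is there.

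The analysis plan is not shown and may define the censoring and competing events. That also stands, so the silence of the primary analysis section on closure or graft is not the main point. But no analysis plan can supply data that the protocol says are not collected.

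Further, infection, antibiotic and safety outcomes are defined up to healing, so their meaning after a graft is unclear, and the record review may capture related serious events. The loss there is less certain than for EQ-5D-5L and resource use. Finally, the article elsewhere describes follow-up as running to four weeks after confirmed healing, which might suggest that healed participants also stop early. The secondary objectives and the week 12 and 26 lists show otherwise for these two measures.

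**Conclusion.** The concern holds in a limited form. The protocol stops data collection after a post-randomisation event without any withdrawal of consent. That conflicts with the intention-to-treat label and, on its natural reading, with the record review on withdrawal. It makes EQ-5D-5L and resource-use data to week 26 missing because of the outcome itself.

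The number affected is unknown; at an assumed 5% it is about 20 of 396. The loss of power is small. Whether the hazard ratio is biased, by how much and in which direction cannot be determined from the article: near nil if surgery is unrelated to healing speed, material only if slow healers are strongly selected or the arms differ. The larger shifts in the table are bounds under assumed rates and selection, not predictions.

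This should be fixed, with moderate confidence. It does not by itself invalidate the primary analysis.

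**What to change.** 1. Replace the sentence that ends data collection. Suggested sense: *participants whose wound is closed, flapped or grafted stop the assessment of healing by secondary intention but remain in follow-up on the existing schedule (safety, antibiotic use, EQ-5D-5L, resource use, record review) unless they withdraw consent.* This concerns data only and leaves clinical decisions untouched.
2. Record the date, type and reason for the procedure, and report counts and reasons by arm.
3. Reconcile the re-excision section with the two statements on ad hoc record review, and say whether clinical withdrawal counts as withdrawal there.
4. Add closure, flap and graft to death in the competing-risk sensitivity analysis, if the analysis plan does not already do so. This is secondary to items 1 to 3: more follow-up alone cannot restore the primary outcome once healing by secondary intention is impossible.

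The cost is a minor amendment and a few extra calls and questionnaires for what is probably a small group. The consent wording, which is not shown, must be checked first. By 31 December 2025, 276 of 396 had been randomised, leaving 120 to enrol plus those still in follow-up. Data may not be recoverable for participants already withdrawn under the present rule, so an early change is worth more than a late one.
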